# Effect of a lifestyle-integrated functional exercise (LiFE) group intervention (sLiFE) to falls prevention in non-institutionalized older adults. Protocol of a randomised clinical trial

**DOI:** 10.3389/fpubh.2023.1304982

**Published:** 2024-01-08

**Keywords:** physical activity, prevention, falls, older adults, balance

## Abstract

**Introduction:**

Personalized programs of integrated strength and balance activities have been shown their effectiveness in falls reduction in the older adults.

**Objective:**

To measure whether a group intervention with the strength and balance principles of the sLiFE program is more effective than standard health advice in reducing the incidence of falls.

**Methods:**

The study will comprise 650 participants with more than 65 years who live at home, observing established inclusion and exclusion criteria. Participants will be randomly assigned in two groups: group intervention (*n* = 325) and standard health advice (*n* = 325). The intervention group will follow the balance and strength activities described in the LiFE program manual. The group intervention will be carried out in groups of 12–14 and will consist of seven one-hour sessions over 12 weeks in health centres. Incidence of falls and quality of life will be assessed as primary outcome variables. Fear of falling and exercise adherence will be analysed as secondary outcome variables.

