### Sample size

3.3

The main variable of the study was used to estimate the sample size, the annual incidence rate of falls in this population. An alpha risk of 0.05 and a beta risk of 0.2 (Power for Chi square 80% and t-test 94%), effect size estimated 0.30 (Cohen D) and 0.01 (V de Cramer) in a two-sided contrast has been accepted, 325 participants in the intervention group and 325 in the control are needed to find differences of ten percentage points as statistically significant between the control group, expected to be 30% [the estimate of falls in people older than 65 years of age (3, 5, 6)] and the intervention group, expected to be 20%. A give up rate of 10% during follow-up has been estimated.

This data has been calculated following the formula for qualitative variables published by Argimon Pallàs et al. (25).

$N=\frac{Za.Ö\;2.p.\left(1-p\right)+ZbÖ\;p1.\left(1-p1\right)+p2.\left(1-p2\right)2}{\left(p1-p2\right)2}$

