#### Stage two

3.6.2

The intervention group (12–14 participants) will be given a brief guide in Spanish from the participant’s manual to advise them in carrying out the activities. The intervention group (*n* = 325) will do the balance activities (tandem stance, tandem walk, one-legged stand, leaning from side to side, leaning forward and backward, stepping over obstacles forwards and backwards, stepping over obstacles sideways) and strength activities (knee bends, sitting down and getting up from normal and low chairs, toe stand, toe walk, heel stand, heel walk, walking sideways, climbing stairs, and tightening muscles), the principles and implementation strategies (26). A total of five one-hour in-person sessions and two follow-up telephone sessions will be held.

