### Statistical analysis

3.9

The study population baseline characteristics will be expressed as means ± standard deviation (SD) for quantitative variables and in frequency distributions for categorical variables. Student’s t-test, chi-square, and Fisher’s exact tests will be applied to find differences in baseline characteristics between intervention and control groups. All analyses of the variables obtained from the questionnaires will be analyzed using the reliability and validity criteria proposed by their authors.

The main analyses will be performed on the intention-to-treat principle, so all randomised subjects will be included in the data analysis set for which the initial assessment was performed. Participants who withdraw or drop out will be asked to be included in follow-up measurements; those lost to follow up will be considered in the full set of analyses as missing data. Detailed modelling of variations between participants and groups will be done in terms of factors such as dose, acceptability, and contextual factors. Using the Chi-square test, we will compare the proportions of subjects who have had a fall in both groups. The comparison of all outcomes between baseline, six and twelve months will be carried out using the two-way repeated measures ANOVA. Logistic regression analysis will be conducted to determine the influence of the different risk factors on falls. Statistics analysed will be performed with SPSS V.25.0 statistical package (SPSS Inc., Chicago, Illinois, United States). *p* values for cut-off values for significance were established at <0.05 (two-tailed). Results were interpreted according *[Cohen]*, who considers small size if Cohen D are between 0.2 ≤ and < 0.5; average effect size if differences are between 0.5 ≤ and < 0.8 and very high effect size if differences are ≥0.8 (38).

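### Sample size and stated tests make no allowance for clustering by session group in the intervention arm; if outcomes correlate within groups, type I error exceeds 5% and power falls below 80%

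*Protocol article*

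**What the plan says.** Section 3.5 of the protocol article describes individual 1:1 allocation. The Abstract (Methods) then states: "The group intervention will be carried out in groups of 12–14". Section 3.6.2 (Stage two) repeats the size: "The intervention group (12–14 participants) will be given a brief guide in Spanish". The comparator is standard health advice, and no grouping of controls is described.

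Section 3.3 sets "An alpha risk of 0.05 and a beta risk of 0.2" and concludes that "325 participants in the intervention group and 325 in the control are needed" to detect 30% against 20% with a fall, allowing for 10% loss. The formula shown there is the ordinary one for two independent proportions.

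Section 3.9 fixes the falls comparison: "Using the Chi-square test, we will compare the proportions of subjects who have had a fall in both groups". It assigns two-way repeated measures ANOVA to the comparison of all outcomes over time and logistic regression to risk factors for falls. The one sentence that touches on variation between groups is: "Detailed modelling of variations between participants and groups will be done in terms of factors such as dose, acceptability, and contextual factors".

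**The concern.** This is an individually randomised trial with group treatment in one arm, a partially nested design. People in a session group share a leader and peers, and the Discussion itself expects the group format to help adherence. If the group influences what its members do, their outcomes may be correlated.

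The chi-square test, the repeated measures ANOVA and the logistic regression, as named, treat the 325 intervention participants as independent. The calculation in section 3.3 does the same. With positive correlation within groups, the intervention arm carries less information than its head count suggests. The efficacy test on falls would then run above its nominal level, and the trial would have less power than stated. Quality of life, the other primary outcome, and the secondary outcomes are exposed in the same way. The formula and the tests are written into the protocol, so this concerns what it fixes and not a detail left to an analysis plan.

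**Working it through.** **Inputs.** From section 3.3: 325 per arm, 30% against 20%, two-sided alpha 0.05, beta 0.2, 10% loss. From the Abstract and section 3.6.2: groups of 12–14. The number of groups is 325/14 = 23.2 to 325/12 = 27.1; groups of 13 give 25. The intraclass correlation (ICC) is not in the documents; 0.01, 0.02 and 0.05 are assumed.

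**1. The plan's own figure.** With a mean proportion of 0.25:

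n = [1.96·√(2·0.25·0.75) + 0.8416·√(0.3·0.7 + 0.2·0.8)]² / 0.10² = (1.2002 + 0.5119)² / 0.01 ≈ 293.1, rounded up to 294 per arm.

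With 10% loss this is 294/0.9 = 327, or 294 × 1.1 = 324. The stated 325 lies between them, so it reproduces under full independence and contains no hidden allowance for clustering. With 325 × 0.9 ≈ 292 analysed per arm, power is 79.8%.

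**2. Design effect, intervention arm only.** DE = 1 + (m − 1)·ICC with m = 13: 1.12, 1.24 and 1.60.

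**3. Type I error of the unadjusted test.** With the same event proportion in both arms, the true variance of the difference is proportional to 1 + DE, while the chi-square test assumes 2. The standard error is too small by the factor √((1 + DE)/2), and the type I error is 2·Φ(−1.96/factor). At ICC 0.05: factor √1.30 = 1.14, and 2·Φ(−1.719) = 8.6%.

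**4. Power of a test that allows for the clustering,** n = 292 per arm:

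Power = Φ[(0.10 − 1.96·SE0)/SE1], with SE0 = √(0.25·0.75·(1 + DE)/n) and SE1 = √((0.21 + 0.16·DE)/n).

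At ICC 0.05: SE0 = √(0.4875/292) = 0.0409, SE1 = √(0.466/292) = 0.0399, power = Φ(0.50) = 69.1%.

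| Assumed ICC | DE | SE factor | Type I error | Power, 292 per arm | n per arm for 80% power, with 10% loss |
|---|---|---|---|---|---|
| 0 | 1.00 | 1.00 | 5.0% | 79.8% | 327 |
| 0.01 | 1.12 | 1.03 | 5.7% | 77.6% | 346 |
| 0.02 | 1.24 | 1.06 | 6.4% | 75.4% | 364 |
| 0.05 | 1.60 | 1.14 | 8.6% | 69.1% | 420 |

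**5. Sensitivity to group size.** At ICC 0.05, moving m from 12 to 14 takes type I error from 8.3% to 8.9% and power from 69.9% to 68.3%. Loss of 10% shrinks a group of 13 to 11.7 analysed members, close to m = 12, so it changes little.

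**6. Health centre as a separate source.** A simulation of 650 individually randomised people in 25 centres (an assumed number), with 30% fallers and no treatment effect, gave rejection rates of 4.8%, 5.1% and 5.0% at centre ICCs of 0.01, 0.02 and 0.05. Centre correlation alone does not inflate the test.

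**The case against.** The strongest reply is that everything depends on an ICC that the documents do not give, and that the text offers reasons to expect a low one. Contact is limited to five in-person sessions and two telephone follow-ups (sections 3.6.2 and 3.6.3), the exercises are meant to be built into daily life, and section 3.6.1 standardises delivery across centres with a manual. At 0.01, the test moves only from 5.0% to 5.7% and power from about 80% to 78%. This stands as a limit on the size of the problem. It does not justify a design and test that are right only at exactly zero, and it does not exclude larger values.

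A second reply is that section 3.9 promises modelling of variation between participants and groups, including contextual factors. That is some stated intent. However, the sentence names no model, does not say that groups means session groups, and leaves the chi-square comparison of falls as it is.

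Three stronger readings are tempting and are not supported:
- A reader might infer that the error rate is wrong outright. It is wrong only if group delivery makes outcomes vary between session groups. For the type I figures, this must happen while the average effect is zero.
- A reader might infer that the planned confidence intervals are wrong. The protocol states none; one can say only that intervals built on the same standard errors would be too narrow.
- A reader might count a shared health centre as a cause. Individuals are randomised, and the documents do not say that centres differ between arms, so centre alone does not inflate type I error.

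**Conclusion.** The point holds in conditional form. Neither the sample size nor the stated tests allow for correlation within the roughly 23 to 27 session groups in the intervention arm. With a positive ICC, the treatment effect's standard error is understated, the nominal 5% chi-square test is too liberal, and a valid test has less than the stated 80% power. Over the assumed range of 0.01 to 0.05 the consequences run from slight to material: at the upper end the false-positive rate is about 1.7 times nominal (8.6/5.0), and nearly 11 points of power are lost (79.8 − 69.1). These sizes rest on the assumed ICC, on groups of about 13, on clustering in one arm only and on large-sample normal approximations. The missing allowance is certain from the text; its numerical effect is not.

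**What to change.** 1. Record the session-group identifier for every intervention participant. Section 3.10 says people are still being invited, so this can begin with the first groups.
2. In section 3.9, replace the plain chi-square test for falls with one prespecified partially nested analysis: a logistic mixed model with a random intercept for session group in the intervention arm only, controls as singletons, and a small-sample correction suited to about 25 groups.
3. Use the same structure in a linear mixed model for quality of life and for the secondary outcomes, in place of the repeated measures ANOVA.
4. In section 3.3, restate power over a stated, assumed range of ICC, for example about 78%, 75% and 69% at 0.01, 0.02 and 0.05 with groups of 13 and 10% loss.

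The cost is one extra data item, revised analysis wording, a less favourable stated power and slightly wider intervals. No extra participants are required if the lower power is accepted openly. Keeping 80% instead would take about 346, 364 or 420 per arm at those three values.

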#### Primary outcome measures

3.7.8

The incidence rate of falls will be estimated based on the intervention and control group. Falls will be recorded using a daily log sent to the study centre monthly. On suffering a fall, participants must provide information about the time, date, injuries and prescribed treatment in relation to the fall, the fall location, and the movement which cause the fall. The person will be interviewed by telephone to correct any lack of data to determine the injuries details and to confirm their health status at this time (7).Quality of life will be measured through the EuroQol 5D questionnaire, validated in Spanish (34). This questionnaire comprises five items (mobility, personal care, daily activities, pain/discomfort, and anxiety/depression) and a self-assessed thermometer of health status.

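### Two unranked primary outcomes (falls and EQ-5D) share one 0.05 cut-off, while the objective, hypothesis and sample size concern falls alone; the passages must be reconciled

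*Protocol article*

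**What the plan says.** **Two primary outcomes.** The Abstract (Methods) says: "Incidence of falls and quality of life will be assessed as primary outcome variables". Section 3.7.8 (Primary outcome measures) repeats the pair: "The incidence rate of falls will be estimated based on the intervention and control group", followed by "Quality of life will be measured through the EuroQol 5D questionnaire, validated in Spanish". Neither place ranks them. Section 3.7.8 describes the EuroQol 5D as five items plus a health thermometer and does not say which score is the outcome.

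**One threshold.** Section 3.9 (Statistical analysis) gives a single criterion: "values for cut-off values for significance were established at <0.05 (two-tailed"). Falls are compared by chi-square on the proportion who have fallen. All outcomes are compared over baseline, six and twelve months by two-way repeated measures ANOVA.

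**Falls alone elsewhere.** Section 3.3 (Sample size) says: "The main variable of the study was used to estimate the sample size, the annual incidence rate of falls". Its error rates ("An alpha risk of 0.05 and a beta risk of 0.2", "in a two-sided contrast has been accepted") go with an expected 30% v 20%, which is a falls comparison. The Abstract's objective and the hypothesis in section 2 also concern falls only. The list of objectives that closes the Introduction covers falls, efficiency, falls by activity level, adherence and fear of falling, but not quality of life.

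**The concern.** A primary outcome is what a trial is judged on. Here EQ-5D has that status in two places, but no hypothesis or objective names it and no sample size is explicitly attached to it. A reader of the final report could not tell whether a significant EQ-5D result with a null falls result is a positive trial. If it were counted as one, the trial would have two chances of a false positive at 0.05 each, and a success by that route would not answer the stated hypothesis on fall prevention.

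**Working it through.** **Step 1. Reproduce the stated sample size, to see which outcome it belongs to.** Inputs from section 3.3: p1 = 0.30, p2 = 0.20, mean p = 0.25, two-sided alpha 0.05 (z = 1.960), power 80% (z = 0.842), dropout 10%.

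n per arm = [1.960 × √(2 × 0.25 × 0.75) + 0.842 × √(0.30 × 0.70 + 0.20 × 0.80)]² / 0.10²

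This gives 294 per arm. Dividing by 0.90 gives 327; multiplying by 1.10 gives 324. Both agree with the stated 325 to within 1%. The 325 per arm is thus a calculation for two proportions of fallers at a full 0.05, with no alpha set aside for EQ-5D. With 10% lost, 325 × 0.90 = 292.5 are analysed per arm and power for falls is 79.9%.

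**Step 2. Family-wise error if either primary outcome suffices.** Inputs: two tests at two-sided 0.05 (section 3.9). The correlation r between the test statistics is not in the document, so a range is assumed.

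- Independent tests: 1 − 0.95² = 0.0975, which is 1.95 times 0.05. The upper bound under any dependence is 0.05 + 0.05 = 0.10.
- Correlated tests: 1 − P(|Z1| < 1.96 and |Z2| < 1.96) under a bivariate normal distribution.

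| r | Family-wise error |
|---|---|
| 0 | 9.75% |
| 0.3 | 9.5% |
| 0.5 | 9.1% |
| 0.7 | 8.3% |
| 0.9 | 7.0% |

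**Step 3. The other possible success rules.**

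- Falls alone decide: error 5%, power about 80%.
- Both must succeed: no inflation, but joint power cannot exceed the 79.9% for falls. Section 3.3 also quotes 94% power for a t-test without naming an outcome. If that refers to EQ-5D, joint power under independence is about 0.80 × 0.94 = 75%.

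**Step 4. Cost of the possible remedies.**

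- Bonferroni split (0.025 each): family-wise error 1 − 0.975² = 4.94% if independent. Power for falls drops from 79.9% to 71.1% at 292.5 analysed. Keeping 80% needs 356 evaluable per arm, or 356 / 0.90 = 396 per arm (792 in all).
- Falls first at 0.05, then EQ-5D at 0.05 only if falls is significant: family-wise error at most 5%, with 325 per arm and 79.9% power for falls unchanged.

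**The case against.** The strongest reply is that a condensed article may leave testing order and alpha allocation to an analysis plan that is not shown, so the lack of a multiplicity rule is not in itself a fault. That stands. But the point does not rest on it. The choice of primary outcome belongs in the protocol, and this article fixes it in two incompatible ways.

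A second reply is that no success rule is written, and that the objective, hypothesis and sample size all point to falls as decisive. That also stands. A reader might infer that EQ-5D alone would count as success and that the trial's alpha is therefore nearly double. The article does not say this. Section 3.3 sets its 0.05 for the falls comparison and section 3.9 gives a cut-off for p values; neither is a claim about a family-wise rate.

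Two further extensions are tempting and unsupported. The two follow-up times do not by themselves add tests, because section 3.9 plans one repeated measures ANOVA across visits, and a group-by-time test there is a single test. A figure of 14.3% (1 − 0.95³) would need the EQ-5D index and thermometer to be tested separately as primary outcomes, which is nowhere stated.

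**Conclusion.** The point holds as a contradiction. Two unranked primary outcomes stand in the Abstract and section 3.7.8, against a falls-only objective, hypothesis and sample size. Its size is conditional: if success on either outcome is enough, the chance of at least one false positive is 9.75% under independence, falling to about 7.0% at correlation 0.9. Both the success rule and the correlation are assumptions. If falls decide, or if both must succeed, there is no inflation. The falls result can be interpreted at 5% in every case, so this should be corrected but does not undermine the main comparison.

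**What to change.** Name falls as the single primary outcome in the Abstract and section 3.7.8. Define it by the measure that section 3.3 is sized on and section 3.9 tests: the proportion with at least one fall, compared by chi-square at two-sided 0.05. Calling it an incidence rate, as sections 3.3 and 3.7.8 do, would name a measure for which the 325 per arm was not calculated, so that label should change too.

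Make one named EQ-5D score at one named time point the first secondary outcome, tested at 0.05 only if the falls comparison is significant. Other EQ-5D results are then descriptive.

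The cost is wording: 325 per arm and about 80% power for falls are unchanged. The small downside is that EQ-5D cannot be claimed if falls is not significant. Section 3.10 describes people still being contacted to take part, so at that stage the change could be made before outcome data accumulate. If the sponsor does want two co-equal primary outcomes, the success rule must be written down and its price in power or sample size accepted.

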**Discussion:**

Physical activity has been put forward as an effective treatment technique for these patients; however, long-term adherence to these programs remains a challenge. Group interventions could reduce dropout rates.

**Conclusion:**

Falls represent a major health problem globally due to the disability they cause in older people. Prevention would help reduce not only their incidence but also the health costs derived from their treatment. Group intervention helps clinicians to save resources and time, being able to attend more people with the same quality of care.

**Clinical trial registration:**

https://clinicaltrials.gov/study/NCT05912088?distance=50&term=NCT05912088&rank=1, identifier NCT05912088.

## Introduction

1

Practitioners and researchers are focused on ageing and frailty, as demonstrated by different initiatives (1, 2). It has been shown that in the population older than 70 years, frailty represent a 5.5 times higher adjusted risk of mortality, a 2.5 times higher risk of new disability, and a 2.7 times higher risk of loss of mobility (3). To reduce frailty, action must be taken on its main risk factor, sedentary lifestyle (4), and the prevention of falls is thus of particular importance; falls are among the five main health problems related with disability in people older than 60 years (5).

Approximately 30% of people aged over 65% and 50% of those over 80 who live in the community have one fall once a year as a minimum (3, 5, 6). Similarly, about 30% of those who fall suffer a new fall in the same year and 10% suffer several falls (7). Falling is, therefore, a risk factor for further falls. Furthermore, Noureldin et al. found that 15% of hospitalised older adults people had a fall within 30 days of discharge (8).

Falls represent a major cause of disability in older adults and over 50% present sequelae (5, 6); half of those suffering a fracture from a fall do not fully recover their previous functional level. Older adults are admitted to hospital for injuries related to falls more frequently and they also present discharges and consecutive readmissions over the following three years (8, 9). Besides, between 32% and 80% of patients who survive hospitalisation after a hip fracture are left with a permanent disability (10), being a 95% of hip fracture cases a result of falls (11). In this regard, it has been observed that physical exercise approaches can reverse the functional disability caused by hospitalisation in older patients (12).

Several studies have demonstrated improvements at cardiovascular and mental levels (dementia), and in psychological stress and quality of life (13, 14). Exercise programs, multifactorial strategies for fall prevention and home interventions diminish falls (6, 15). Other systematic reviews and meta-analyses which have found multifactorial interventions, including exercise, postulated as the most effective, with a single intervention with exercise also showing significant effects are in this line. The literature suggests that exercise is the best approach for preventing falls at this population, but this could be influence by the exercise component selected (16, 17). Other structured training programs aim to improve muscle strength and balance, for example, the Otago Exercise Program (18). Nevertheless, they often do not generate long-term change, participation and adherence (19, 20); however, physical activity has shown numerous benefits (21). A review concluded that multicomponent group exercise and exercise at home, as well as safety interventions at home, diminish the rate and the risk of falls (22).

The LiFE study (Lifestyle-integrated Functional Exercise) intervention stood out as achieving the best results in preventing falls with a reduction of 13% (23). It is a personalized program which has demonstrated its effectiveness improving balance, strength, and physical activity, while falls in older adults were reduced by incorporating exercise activities into their daily activities. This program shown a clinically significant reduction of 31% in fall rate in comparison to the control program. A 30% in falls reduction is like most interventions currently recommended for preventing falls in clinical guidelines. It has recently been suggested in a pilot study that LiFE could be effective administered in a group setting in comparison to an individual intervention (24).

This project aims to compare the standard health advice to the original LiFE program implemented in a group (sLiFE), with the aim of facilitating large-scale implementation with lower use of resources and verifying effectiveness in terms of fall rates, physical activity, and profitability.

The objectives will be to assess if a group intervention implementing the sLiFE program principles reduces fall rates compared to standard advice; to assess whether fall prevention is more efficient in the group intervention than standard individual recommendations; to measure the incidence rate of falls according to participants’ level of physical activity; to assess medium- and long-term adherence to the exercise program and to find out the participants’ fear of falling.

